**Sixth meeting:**

**Participants start taking metformin or placebo pills twice a day for one month**

The physician will

- Collect information on side effects.
- Count the non used pills to verify compliance.
- Provide the pills for the next 6 months. Participants shall assume two pills per day (for a total of 1700 mg of metformin in the intervention arm); it is recommended to take the pill during the main meals (e.g. one at breakfast and one at dinner, or one at lunch and one at dinner)
- Remember not to increase the dose and not throw away the unused pills
- Stop taking the pills for a few days in case of surgical interventions, anaesthesia, or radiological examinations requiring contrast means
- Arrange the next meeting
- Arrange the dates of common lunches or dinners and for physical exercise meetings for participants randomized in the active lifestyle intervention group

**7th and 8th meeting:**

**Participants, in absence of major side effects, receives the pills for the next 6 months. If the full dose is not tolerated participants are invited to go back to a single pill per day.**

**9th meeting:**

**After 12 months of taking metformin or placebo at full dose, participants are invited for a new clinical visit, eligibility check, anthropometric measurements and blood and urine sample.**

In case of contra-indication to continue metformin treatment (e.g. for intervening diagnosis of renal insufficiency or major cardiovascular, metabolic or respiratory diseases) participants will be recommended to interrupt the drugs and to continue only the dietary intervention. The participant's general practitioner will be informed. If there are no contra-indications the participants will be given the pills for the next 12 months. At every meeting participants are invited to fill in a food frequency and physical activity questionnaire; this will allow the study dietician to reinforce lifestyle recommendations for those randomized in the active lifestyle intervention group. Participants randomized in the intervention group not showing significant improvements will be offered special teaching sessions.

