**Baseline requirements**

Participants will be requested:

- to sign the informed consent to participate in the study and to follow the prescribed treatment and lifestyle changes, to provide information on their health status and intervening diseases, and to allow the study officials to contact their treating physicians, to consult clinical notes and to examine blood samples for metabolic, genetic and epigenetic studies, even after the end of the active intervention period
- to fill in a questionnaire on medical history and risk factors (the EPIC-Italy questionnaire)
- to undergo an anthropometric visit (height, weight, waist and hip circumference, blood pressure, body fat and lean mass measured with Tanita impedance device, at baseline and after 1 year)
- to donate a 20 ml blood sample (at baseline and after 1 year)
- to fill in 24h dietary and exercise recall forms (either directly or on the phone) every 2 months in randomly chosen days.

Participants will be informed that they can retire from the study at any moment, but recommended not to do so because it would damage the interpretation of results.

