**Prescriptions:**

A) 2 tablets per day, one at breakfast (or lunch) and one at dinner, of either metformin (two 850 mg tablets/day) or placebo (two identical tablets) according to the blind assignment. In case of gastrointestinal discomfort occurring after randomization participants will be asked to continue with a single tablet. In our pilot trial such side effect occurred in 10 out of 80 participants: 7 of them stopped taking the pill and 3 continued at half the dose. Subjects stopping taking the pills will be kept in the study, but we will increase the study size by 10% to partly compensate the power loss.

B) participation in the life-style intervention activities. All participants will receive general lifestyle recommendations for the prevention of cancer and cardiovascular diseases, including smoking cessation counselling, and those randomized in the life-style intervention group will be offered to participate to four kitchen courses and will then be invited monthly for lunch or dinner, physical activity sessions, and nutritional counselling to strengthen their commitment over the whole duration of the study. Such a schedule proved to be sufficient to obtain significant reduction of body weight (3 Kg on average after one year) and of MetS parameters in our ongoing randomized trial of lifestyle modification in breast cancer patients.

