**Participants having demonstrated an adequate compliance and no or trivial side effects will be randomized**

## **RANDOMIZATION**

**Fifth meeting:**

**Participants assume a placebo or metformin (850 mg) pill per day for 30 days.**

The physician will:

- Provide the pills for the next 30 days
- Remember not throwing away the unused pills
- Arrange the next meeting (that will be also remembered through an SMS)
- Arrange the dates of kitchen courses for participants randomized in the active lifestyle intervention group

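### The one-year assessment is timed by 12 months at full dose, which leaves people who stop or step down without a defined visit and does not match the dispensing schedule

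*Protocol*

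**What the plan says.** **The visit.** Under the 9th meeting, the Operative protocol says: "After 12 months of taking metformin or placebo at full dose, participants are invited for a new clinical visit". The visit includes an eligibility check, anthropometry, and blood and urine samples. It is the only blood and urine collection after baseline that the Operative protocol schedules. The later yearly meetings name eligibility, weight and waist, and the exit visit names a clinical visit and anthropometry.

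**The same sample in the Methodology.** Baseline requirements asks participants "to donate a 20 ml blood sample (at baseline and after 1 year", with no condition on dose. Blood examinations places the MetS markers at baseline and one year. Study design lists change in MetS prevalence and its components as a secondary outcome, and Analysis makes the main analyses intention to treat.

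**People who stop or step down.** Prescriptions keeps people who stop the tablets in the study. It reports a pilot in which 10 of 80 had gastrointestinal discomfort: "7 of them stopped taking the pill and 3 continued at half the dose".

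**The meetings before the visit.** At the 5th meeting: "Participants assume a placebo or metformin (850 mg) pill per day for 30 days". The 6th meeting's heading reads "Participants start taking metformin or placebo pills twice a day for one month", but its task list reads "Provide the pills for the next 6 months". The joint entry for the 7th and 8th meetings reads in part: "receives the pills for the next 6 months. If the full dose is not tolerated participants are invited to go back to a single pill". The 9th meeting hands out a 12-month supply, whereas Organization in the Methodology has refills every six months.

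**The concern.** There are two separate problems.

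First, the visit rule depends on something that happens after randomisation and may be affected by treatment. Someone who stops, or goes back to one pill, does not complete 12 months at full dose, so the rule gives them no date. Someone who pauses reaches it late. If gastrointestinal intolerance is commoner on metformin than on placebo, omitted or delayed visits would be unequal between arms. The one-year MetS comparison would then drift towards people who tolerated full treatment, although the plan calls for intention to treat. The same visit supplies the second half of the biobank pair and the scheduled check for contraindications.

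Second, the protocol gives more than one answer to when this visit takes place, because the supply intervals leading up to it do not add up to the stated time.

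**Working it through.** **Inputs.** One month on a single pill follows randomisation (5th meeting). The 6th meeting starts two pills a day and mentions both one month and six months. The 7th and 8th meetings each give six months, reading the joint heading as applying to both. The stated trigger is 12 months at full dose (9th meeting). A 30-day metformin run-in lies between the baseline blood sample and randomisation (3rd and 4th meetings).

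**Assumptions.** The 5th meeting is month 0, so full dose starts at month 1. For the dispensing readings, each meeting falls when the previous supply ends.

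**Formulas.** Months after randomisation = 1 + months at full dose. Months after baseline blood ≥ months after randomisation + 1.

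| Reading | Months at full dose at 9th meeting | Months after randomisation | Months after baseline blood (at least) |
|---|---|---|---|
| Trigger as stated | 12 | 1 + 12 = 13 | 14 |
| 6th-meeting heading (one month) | 1 + 6 + 6 = 13 | 1 + 13 = 14 | 15 |
| 6th-meeting task list (six months) | 6 + 6 + 6 = 18 | 1 + 18 = 19 | 20 |

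The stated 12 months is reproduced by neither dispensing reading. Under the task-list reading the 12-month point falls at the 8th meeting (6 + 6 = 12; month 13), which is described only as a dispensing visit. Under the heading reading the gap is one month, but the six-month supply at the 6th meeting is then unexplained.

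**Distance from one year after randomisation.** 13 − 12 = 1 month for the stated trigger, 14 − 12 = 2 for the heading reading, and 19 − 12 = 7 for the task-list reading.

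**How many people could be affected.** In the pilot 10/80 = 12.5% stopped or halved (7/80 = 8.75% and 3/80 = 3.75%). If that rate held in 1,000 metformin participants, 0.125 × 1,000 = 125 would not meet the trigger literally. This only illustrates scale. The pilot count is not split by arm, no placebo rate is given, and this trial removes intolerant people in a run-in before randomisation. The document does not say whether the pilot did the same.

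**The case against.** The strongest reply is that the 9th meeting merely describes the typical participant. Nothing excludes anyone from it. The request for one-year blood goes to all participants, those who stop stay in the study, and stepping down is described within the 7th and 8th meetings, so those people are still in the visit sequence. The budget has 40,000 Euro for baseline and 12-month exams at 20 Euro a person, and 40,000 / 20 = 2,000 people. Visit windows and the handling of people off treatment often belong in an analysis plan. The stated trigger is also only one month from one year after randomisation.

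Most of this stands, and it rules out three stronger readings that a reader might infer:

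- **That people who stop or step down never reach the visit.** This follows only from a literal reading of the trigger. The document contains a conflict, not a stated exclusion.
- **That the one-year effect would be overstated by about 14%.** That figure is just 1/0.875 = 1.14. It assumes that the pilot rate applies to metformin, that everyone affected is lost, and that they gain nothing even at half dose. The document supports none of these.
- **That the primary outcome is compromised.** Follow-up rests mainly on active contact, clinical records, hospital discharge data, the death index and cancer registries. Diabetes is 219 of the 175 + 119 + 219 = 513 expected events and can be defined by fasting glucose, so a link to this sample is conceivable. The document does not say that these values feed the endpoint.

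The reply does not remove the defect. The Operative protocol is what sites follow, and its trigger disagrees with the Methodology for those at most risk of being missed. An analysis plan cannot recover samples that were not taken. The two supply lengths at the 6th meeting also cannot both set the date of the next one.

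**Conclusion.** The point holds as a contradiction with a practical risk. The full-dose trigger conflicts with a one-year sample asked of all participants and with keeping people who stop or step down in the study. Read literally, it leaves them without a defined one-year assessment. If sites acted on it, the one-year MetS outcome would move away from intention to treat, by an amount the document does not allow one to estimate.

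The timing conflict can be stated exactly, given that meetings follow the end of each supply: 13 or 18 months at full dose against the stated 12. The 18-month figure is one reading of the supplies, not an established date. The gap between the stated trigger and one year would be minor on its own, but a possible seven-month gap is not.

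Severity is moderate. A named secondary outcome, the paired biobank sample and the scheduled recheck are affected.

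**What to change.** State in the Operative protocol that the one-year outcome assessment (anthropometry, blood, urine) is timed from randomisation, with a stated window, and applies to every randomised participant whether on full dose, on one pill or off pills. State that the one-year MetS outcome is analysed in all randomised.

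Reconcile the dispensing and meeting intervals in the 6th to 9th and yearly meetings, and the six-monthly refills in Organization, with that date. Which supply interval or dose rule is right is for the investigators, and none is proposed here.

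The cost is protocol wording, plus some effort to bring back people who are off pills. The one-year visit and sample are already planned, and the laboratory exams are already in the budget.

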**Further yearly meeting:**

**To check eligibility, body weight and waist circumference, and to provide the pills for the next 12 months**

Every meeting will be preceded by a telephone remind (SMS)

At each meeting and in a random day every two months all participants will be invited (through SMS or telephone) to fill in a 24h food frequency and physical activity diary

For participants randomized into the dietary intervention group the meetings will usually be arranged in the same days of the kitchen courses and common meals.

Participants who for whatever reason decide to interrupt the study will be invited for a final clinical visit and anthropometric measurement

### c. Funding

#### Amount of funding necessary

The estimates are largely based on what we spent for our ongoing life-style intervention study of 2,000 breast cancer survivors.

#### Drug

On average participants will be treated for 4 years with either Metformin or placebo. Our pharmacist has estimated that we will need 400,000 Euro to prepare Metformin and placebo for the whole study. Metformin is very cheap (less than 5 Euro per month of treatment) but companies are not interested to sponsor a study.

#### Food and kitchen activities

On average participants randomized in the intervention group will receive 4 full-day kitchen courses and will be invited monthly for lunch or dinner with short kitchen courses for 4 years (10 months per year), for a total of 40,000 meals. In previous trials we spent 7 Euro per meal. Taking into account inflation but also some scale economy the total expenditure for food and kitchen activities will be  $8 \times 40,000 = 320,000$  Euro (125,000 about for food purchase).

#### Laboratory activities

Laboratory costs are mainly for basic clinical chemistry and insulin, growth factors, and inflammatory cytokines. For epigenetic tests we have applied to other sources.

#### Equipment

|               |             |
|---------------|-------------|
| -80°C Freezer | Euro 20,000 |
|---------------|-------------|

#### Consumables

|                                                           |                |
|-----------------------------------------------------------|----------------|
| Metformin                                                 | 400,000        |
| Vials for biological bank (16 per person)                 | 10,000         |
| Baseline and 12 month laboratory exams (20 Euro x person) | 40,000         |
| Hormonal exams                                            | 45,000         |
| Subtotal Consumables                               | 495,000 |

|                                                                                                                |        |
|----------------------------------------------------------------------------------------------------------------|--------|
| Travels (participation to conferences/congress to present data and local trips to organize recruitment) | 10,000 |
|----------------------------------------------------------------------------------------------------------------|--------|

|                                         |       |
|-----------------------------------------|-------|
| Publication costs (journal fees) | 5,108 |
|-----------------------------------------|-------|

|                                      |           |
|--------------------------------------|-----------|
| Personnel (see attached form) | 1,340,500 |
|--------------------------------------|-----------|

|                             |            |
|-----------------------------|------------|
| Indirect costs (20%) | 374,121.60 |
|-----------------------------|------------|

|                                                      |                |
|------------------------------------------------------|----------------|
| Subcontract for kitchen activities and food purchase | 234,000        |
| Certificates of Financial Statement (CFS)            | 21,270         |
| Subtotal subcontracting costs:                | 255,270 |

|              |                     |
|--------------|---------------------|
| Total | 2,499,999,60 |
|--------------|---------------------|

|                                     | Cost Category                        | Month 1-18 | Month 19-36 | Month 37-54 | Month 55-60 | Total (M1-60) |
|-------------------------------------|--------------------------------------|------------|-------------|-------------|-------------|---------------|
| Direct Costs:                | Personnel:                    |            |             |             |             |               |
|                                     | PI                       | 20,000.00  | 60,000.00   | 60,000.00   | 20,000.00   | 160,000.00    |
|                                     | Senior Staff                         | 260,000.00 | 260,000.00  | 260,000.00  | 120,000.00  | 900,000.00    |
|                                     | Post docs                            | 57,500.00  | 57,500.00   | 57,500.00   | 22,000.00   | 194,500.00    |
|                                     | Students                             |            |             |             |             |               |
|                                     | Other                                | 20,000.00  | 25,000.00   | 25,000.00   | 16,000.00   | 86,000.00     |
|                                     | Total Personnel:                     | 357,500.00 | 402,500.00  | 402,500.00  | 178,000.00  | 1,340,500.00  |
|                                     | Other Direct Costs:           |            |             |             |             |               |
|                                     | Equipment                            | 6,000.00   | 6,000.00    | 6,000.00    | 2,000.00    | 20,000.00     |
|                                     | Consumables                          | 125,000.00 | 160,000.00  | 160,000.00  | 50,000.00   | 495,000.00    |
|                                     | Travel                               | 2,500.00   | 2,500.00    | 2,500.00    | 2,500.00    | 10,000.00     |
|                                     | Publications, etc                    |            |             |             | 5,108.00    | 5,108.00      |
|                                     | Total Other Direct Costs:            | 133,500.00 | 168,500.00  | 168,500.00  | 59,608.00   | 530,108.00    |
|                                     | Total Direct Costs:                  | 491,000.00 | 571,000.00  | 571,000.00  | 237,608.00  | 1,870,608.00  |
| Indirect Costs (overheads):  | Max 20% of Direct Costs              | 98,200.00  | 114,200.00  | 114,200.00  | 47,521.60   | 374,121.60    |
| Subcontracting Costs:        | Audit                                | 6,700.00   | 7,350.00    | 7,220.00    |             | 21,270.00     |
|                                     | Kitchen activities and food purchase | 70,000.00  | 70,000.00   | 70,000.00   | 24,000.00   | 234,000.00    |
| Total Subcontracting Costs:  |                                      | 76,700.00  | 77,350.00   | 77,220.00   | 24,000.00   | 255,270.00    |
| Total Costs of project:      | (by reporting period and total)      | 665,900.00 | 762,550.00  | 762,420.00  | 309,129.60  | 2,499,999.60  |
| Requested Grant: | (by reporting period and total)      | 665,900.00 | 762,550.00  | 762,420.00  | 309,129.60  | 2,499,999.60  |

**Time table and milestones**

1-18 Month: Formalisation of the operative protocol, Start of recruitment

19-36 Month: Recruitment, Start of follow-up, Quality control checks, Second blood sample

37-54 Month: Follow-up, Hormonal and cytokines exams, Ad-interim analyses

55-60 Month: End of follow-up, Statistical analysis

|                                                                                                                                      |            |
|--------------------------------------------------------------------------------------------------------------------------------------|------------|
| For the above cost table, please indicate the % of working time the PI dedicates to the project over the period of the grant: | 40% |
|--------------------------------------------------------------------------------------------------------------------------------------|------------|

[name] "PI" will follow all the phases of the project. He will be personally involved in the counselling of participants and in the quality control of procedures and outcomes.

**iii. Budget - Table 2**

| „key intermediate goal“, as defined in section 2.           | Estimated % of total requested grant | Expected to be completed on month : | Comment                                                                                                                                                       |
|--------------------------------------------------------------------|---------------------------------------------|--------------------------------------------|----------------------------------------------------------------------------------------------------------------------------------------------------------------------|
| formalization of the operative protocol, start recruitment         | 28%                                         | 18                                         | In this first period we have to implement and test strategies for efficient recruitment                                                                              |
| complete recruitment, start follow-up, compliance monitoring       | 31%                                         | 36                                         | Active follow-up will start as soon as the first recruited persons reach one year of treatment                                                                       |
| follow-up, biochemical analyses                                    | 30%                                         | 54                                         | Metabolic and hormonal analyses will be used to proceed to a first comparison between the four arms of the study                                                     |
| end follow-up, quality control of end-points, statistical analysis | 11%                                         | 60                                         | During all the study any effort will be made to obtain clinical and pathological reports of the diagnosed diseases. The main analyses will be by intention to treat. |
| Total                                                       | 100%                                 |                                            |                                                                                                                                                                      |

